### Data management {19}

A CONSORT diagram tracking log will be used to track the number of participants that were pre-screened, consented, cleared for treatment, and completed the study, as well as withdrawals. Case report forms containing hard copies of data will be stored within a locked filing cabinet in a secure, locked room. Data from case report forms, including clinical measures and laboratory data, will be entered digitally and stored on HIPAA-compliant servers. REDCap will be used for secure collection and storage of digital survey and questionnaire data. Upon completion of the clinical trial, study documents will be retained for a minimum of seven years.

### Confidentiality {27}

Participant identification codes are assigned at the time of screening. PIs and study coordinators have access to personal identifiers of enrolled participants and medical records through their dual roles as researchers and care providers.

### Plans for collection, laboratory evaluation, and storage of biological specimens for genetic or molecular analysis in this trial/future use {33}

No biological specimens were collected in this trial.

### Case report form

For each consented participant, a case report form will be generated that summarizes screening and study data, including deidentified hard copies of clinical measures. Participants will be identified by their alphanumeric identifier on this form to maintain confidentiality. Upon completion of the study, case report forms will be maintained for a minimum of seven years.

## Statistical methods

### Statistical methods for primary and secondary outcomes {20a}

The first objective of this study is to examine baseline (i.e., pre-treatment) associations between anhedonia and psychosis and neural and molecular responses to rewards. Associations between clinical measures and mechanistic outcomes will be estimated via correlation analysis. The second objective is to evaluate the experimental effects of estradiol versus placebo on clinical outcome measures and mechanistic outcomes. Mixed effects models will be used to examine the effects of time, treatment group, and their interaction on clinical outcomes (four timepoints, random intercept and slope) and neural and molecular outcomes (two timepoints, random intercept only), with age as a covariate. A separate model will be generated for each clinical outcome measure (anhedonia and psychosis) and each neural and molecular outcome (activation during reward anticipation and BP_ND_ and task-related ΔBP_ND_ for striatal regions of interest). Exploratory whole-brain analyses will also be conducted for fMRI activation during reward anticipation. Within the estradiol treatment group only, we will examine how biomarkers of reward response predict changes in clinical outcome measures. We will examine intercorrelations between anhedonia or psychosis and neural and molecular reward response, using residualized gain scores to quantify changes in clinical measures. We will also use mixed effect models to examine how changes in neural and molecular reward response predict variability in clinical outcome trajectories, with a separate model for each clinical outcome and each neural and molecular change score. Maximum likelihood estimation will be used in all mixed effect models to accommodate missing data (e.g., SAS proc mixed). When multiple comparisons are conducted to test a hypothesis, appropriate correction will be applied to achieve a corrected *p*-value of 0.05. For clinical outcome hypotheses, both a per-protocol and an intent-to-treat analytic approach (e.g., utilizing all available data, even for participants who did not finish treatment to completion) will be used. For mechanistic hypotheses, a per-protocol approach will be used, including only participants who completed the baseline PET-MR scan, 3 weeks of estradiol treatment, and the post-treatment PET-MR scan.

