### Eligibility criteria {10}

The study will include unmedicated, perimenopausal outpatient women ages 44–55 who are in late perimenopause and experiencing anhedonia and/or psychosis symptoms with onset coinciding with perimenopausal menstrual irregularity. To determine participant eligibility, women will undergo initial online and phone screening, the structured clinical interview for the DSM-5 (SCID-5), laboratory testing, and a pelvic exam/PAP test (or a medical records review for an exam within 3 years). Participants must meet the following inclusion criteria to be enrolled in the study:44–55 years old, unmedicated, naturally perimenopausal woman in stage −1 of the Stages of Reproductive Aging Workshop (STRAW) criteria [36, 37]At least mild perimenopausal-onset anhedonia (SHAPS≥20) (Snaith et al. [38])Absent-to-moderate perimenopausal-onset psychosis spectrum symptoms as measured by the Brief Psychiatric Rating Scale (BPRS-Positive Symptom Subscale Score between 6 and 17) (Hafkenscheid [39]; Overall & Gorham [40])

Dimensional measures of anhedonia and psychosis severity are used to stratify participants. With respect to stratification, equal numbers of participants will be recruited into each of the following four strata:Mild-to-moderate anhedonia + absent-to-mild psychosisMild-to-moderate anhedonia + moderate psychosisHigh anhedonia + absent-to-mild psychosisHigh anhedonia + moderate psychosis

Mild–moderate anhedonia severity is defined in this trial as Snaith–Hamilton Pleasure Scale (SHAPS [38]) scores between 20 and 36, and high anhedonia severity is defined as SHAPS>36 (using the ordinal scoring of Franken et al. [41]). There is no widely accepted clinical cut-off on the SHAPS, though a meta-analysis by Trøstheim and colleagues (2020) [42] reported that caseness is indicated by scoring more than 1.96 SDs above the general population, which would correspond to a SHAPS score of 25 or greater (see also Alsayednasser and colleagues [43]). However, in this trial, a SHAPS score cutoff of >20 was used to indicate at least mild, clinically impairing anhedonia, consistent with the cutoff used in the NIMH Fast-Fail Trial for Mood and Anxiety Disorders [38, 44]. The SHAPS has shown adequate psychometric properties in clinical and non-clinical samples [45], and ROC analyses suggest that a SHAPS score of ≥ 20 corresponds to clinically significant anhedonia from a general population sample [38].

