### Sample size {14}

For the first study objective, correlation analyses will be used to examine associations between baseline clinical measures (anhedonia and psychosis) and neural markers (striatal BOLD activation and baseline/reward-related dopamine release). Power analysis suggests that a sample of 85 participants will yield approximately 80% power to detect small-to-medium effects (smallest detectible *r*=.27) at *α*=.05, which is consistent with our in-house pilot data. With respect to the study’s second objective, longitudinal mixed models will be used to examine the effects of estradiol versus placebo on (1) symptom trajectories measured across four timepoints and (2) neural/molecular markers across two timepoints. A sample of 85 participants will yield 80% power to detect small-to-medium effects, with the smallest detectible effect *f*^2^=.05 for clinical outcomes and *f*^2^=.07 for brain changes. To determine associations between changes in symptoms and changes in neural/molecular reward response in the estradiol treatment group, intercorrelations will be examined in primary analyses. A sample of 43 participants will yield 80% power to detect medium-to-large effects, with the smallest detectible effect size of *r*=.41.

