## Data collection and management

### Plans for assessment and collection of outcomes {18a}

The primary clinical outcomes measures will examine anhedonia and psychosis-spectrum symptoms at treatment baseline, week one, week two, and the end of treatment (week 3). The Snaith–Hamilton Pleasure Scale (SHAPS) [38], a 14-item self-report questionnaire assessing hedonic behaviors with a score range of 14–56, will be used as a dimensional measure of anhedonia. The Brief Psychiatric Rating Scale, an 18-item, rater-administered scale measuring psychotic symptoms and anti-psychotic treatment response, will be used as a dimensional measure of psychosis [39, 40]. A psychosis subscale score will be calculated for primary analyses, consisting of scores from four items: conceptual disorganization, suspiciousness, hallucinations, and unusual thought content.

Additional measures will be collected to assess psychological and physiologic symptoms associated with the perimenopausal transition. Measures include the following:Inventory of Depression and Anxiety Symptoms (IDAS-II [56]), a 64-item self-report measure with good psychometric properties that has been validated for use with reproductive mood disorder samplesClinical Global Impression (CGI) scale [57]: assessment of functional impairment to be collected at pre-treatment, week one, week two, and post-treatmentLife Events Survey [58]: survey of stressful life events that may moderate effects of mood symptoms [59]Green Climacteric Scale [60]: 21-item gold-standard self-report measure for assessment of climacteric symptoms (vasomotor, somatic, anxiety, depression)Pittsburgh Sleep Quality Index (PSQI [61]): 9-item self-report questionnaire measuring sleep quality/patterns in older adultsDSM-5 Self-Rated Level 1 Cross-Cutting Symptom Measure—Adult [62]: self-report questionnaire assessing symptoms relevant across different mental health diagnosesThe 7-item anxiety scale (GAD-7) [63]: brief self-report anxiety scalePatient Health Questionnaire (PHQ)-9 [64]: brief 9-item questionnaire to assess depression severityWorld Health Organization Disability Assessment Schedule 2.0 [65]: self-report assessment of functioning across six domains (cognition, mobility, self-care, social interaction, life activities, participation)

These measures will be used in secondary and/or sensitivity analyses to examine the effect of covariates (in particular, climacteric symptoms, sleep quality, stressful life events).

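### The Objective 1 baseline correlations name no covariate, although the same clinical and brain outcomes are adjusted for age in the randomised Objective 2 models

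*Protocol article*

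**What the plan says.** All references are to the protocol article.

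- **Objective 1, analysis** (Statistical methods for primary and secondary outcomes {20a}): "Associations between clinical measures and mechanistic outcomes will be estimated via correlation analysis". No covariate, partial correlation or regression is mentioned.
- **Objective 1, power** (Sample size {14}): "correlation analyses will be used to examine associations between baseline clinical measures (anhedonia and psychosis) and neural markers". The section states that "a sample of 85 participants will yield approximately 80% power to detect small-to-medium effects", with a smallest detectable r of .27 at α = .05. This is a calculation for a simple correlation.
- **Objective 2, analysis** (section {20a}): the mixed models cover the clinical outcomes and "neural and molecular outcomes (two timepoints, random intercept only), with age as a covariate". The brain outcomes are striatal activation during anticipation, baseline binding potential and its task-related change, which are also the mechanistic measures of Objective 1.
- **Other covariates** (Plans for assessment and collection of outcomes {18a}): the additional questionnaires are for "secondary and/or sensitivity analyses to examine the effect of covariates (in particular, climacteric symptoms, sleep quality, stressful life events"). Age is not on that list.
- **Population** (Eligibility criteria {10}): "unmedicated, perimenopausal outpatient women ages 44–55 who are in late perimenopause".

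**The concern.** Objective 1 is a cross-sectional, observational association. If age is related both to symptom severity and to the striatal measure, part of any correlation between the two reflects age and not the reward mechanism that the hypotheses describe. Nothing in the design balances age across levels of SHAPS or BPRS.

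In Objective 2, randomisation balances age between arms in expectation, so age there mainly serves precision. Having chosen age as a relevant covariate for both kinds of outcome, the plan applies it where confounding is the lesser worry and does not mention it where confounding is the greater one.

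At stake is the interpretation of the Objective 1 correlations, which test directional hypotheses linking anhedonia and psychosis to striatal activation and dopamine release. There is also a smaller matter of precision: if age explains variance in the brain measure but is unrelated to symptoms, leaving it out gives some power away.

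**Working it through.** **Inputs from the article:** n = 85, r = .27, α = .05 and about 80% power (Sample size {14}). Sidedness is not stated. **Not in the article:** any correlation of age with SHAPS, BPRS, activation or binding potential. Those values below are assumptions.

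**1. The plan's own figure.** By Fisher z, with k covariates partialled out,

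power = Φ(atanh(r)·√(n − k − 3) − z), where atanh(.27) = .2769.

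With k = 0, √82 = 9.055 and the product is 2.507.

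- One-sided: Φ(2.507 − 1.645) = 80.6%. This reproduces the stated figure.
- Two-sided: Φ(2.507 − 1.960) = 70.8%. This does not.

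The choice of sides is a separate matter. Both are carried forward here only to price the adjustment.

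**2. Cost of adjusting for age if age is unrelated to either measure.** With k = 1, √81 = 9 and the product is 2.492.

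| | Power, k = 0 | Power, k = 1 | Detectable r, k = 0 | Detectable r, k = 1 |
|---|---|---|---|---|
| One-sided | 80.6% | 80.1% | .268 | .269 |
| Two-sided | 70.8% | 70.3% | .300 | .302 |

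The cost is about 0.5 percentage points.

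**3. What omitting age could do (assumed correlations).** If symptoms and brain measure are unrelated given age, the correlation induced is the product r(age, symptom) × r(age, brain). The two-sided rejection rate at n = 85 is

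Φ(atanh(r)·√82 − 1.96) + Φ(−atanh(r)·√82 − 1.96).

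For .2 × .3, r = .06 and atanh(.06)·9.055 = .544. The two terms are Φ(−1.416) = .078 and Φ(−2.504) = .006, which sum to about 8.5%.

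The last column below asks a different question: what an observed r of .27 becomes after adjustment, for age correlations of the same sign. The formula is (.27 − ab)/√((1 − a²)(1 − b²)), where a and b are the two age correlations.

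| Assumed age correlations | Spurious r | Rejection at nominal 5% | Observed .27 becomes |
|---|---|---|---|
| .1 and .1 | .01 | 5.1% | .263 |
| .2 and .2 | .04 | 6.5% | .240 |
| .2 and .3 | .06 | 8.5% | .225 |
| .3 and .3 | .09 | 12.9% | .198 |
| .3 and .4 | .12 | 19.4% | .172 |

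**4. Precision, a different scenario.** Suppose age is unrelated to symptoms but explains 4%, 9% or 16% of the brain measure. A true r of .27 then becomes a partial r of .27/√(1 − R²) = .276, .283 or .295. Two-sided power with k = 1 is 72.1%, 74.5% or 78.0%, against 70.8% unadjusted.

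**The case against.** The strongest reply is that this is silence in a condensed article. Correlation analysis does not mean unadjusted correlation: a partial correlation is also a correlation, and a full protocol or analysis plan could name age. The two objectives ask different questions, and nothing obliges their covariates to match. The covariate list in section {18a} is introduced as particular examples, so it need not be complete.

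Much of that stands. A reader might infer that the article rules out age adjustment, and it does not. However, the method and the power calculation both describe a correlation with no covariate, while the same section states the covariate for the other objective. The change proposed is a better choice of primary estimate, which goes beyond asking for a missing detail.

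Three further points limit the size of the concern, and all are accepted.

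- A reader might take the age range as spanning the menopause transition. Eligibility is confined to late perimenopause (STRAW stage −1), and one stage within an 11-year age band limits how far age can track either variable.
- A reader might take the upper rejection rates as evidence of bias. They follow only if both age correlations are material, and the article documents neither. With weak correlations (.1 and .1) the inflation is negligible.
- The hypotheses for anhedonia and psychosis have opposite signs for striatal activation. If age moved both symptoms in the same direction, it would favour one of those hypotheses and work against the other. An age effect would not uniformly look like confirmation.

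**Conclusion.** The point holds in a limited form. Objective 1 is specified and powered as correlation with no named covariate, while age is adjusted for in the randomised models of the same outcomes, where confounding is less of a concern.

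The possible effect ranges from negligible to moderate: a spurious r of .01 to .12 and rejection of about 5% to 19% at nominal 5%. That range rests entirely on assumed age correlations between .1 × .1 and .3 × .4, at n = 85 and two-sided. The documents do not support saying that the Objective 1 results will be biased. They support saying that a plausible source of bias can be removed at almost no cost, with a covariate the plan already uses. Importance is low.

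**What to change.** In section {20a}, state that each primary Objective 1 association is a partial correlation between the baseline symptom score and the striatal measure, adjusted for age. A linear regression of the striatal measure on SHAPS or BPRS psychosis score with age as a covariate gives the same test. Report the unadjusted r as a sensitivity result, so that readers can see what age contributes. Amend the Objective 1 sentence in Sample size {14} to say that the detectable r is a partial correlation.

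The cost is one degree of freedom and a line of wording. If age is unrelated to both measures, power at r = .27 falls by about 0.5 percentage points and the detectable r rises by .001 to .002. No new data are needed: age is known for every participant from eligibility. Recruitment is planned to run to the end of 2026, and the change should be recorded before the Objective 1 data are analysed.

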## Abstract

**Background:**

The perimenopausal transition is accompanied by psychiatric symptoms in over 10% of women. Symptoms commonly include depressed mood and anhedonia and less commonly include psychosis. Psychiatric symptoms have been linked to the depletion and/or variability of circulating estradiol, and estradiol treatment reduces perimenopausal anhedonia and psychosis in some women. Estrogen fluctuations may disrupt function in the mesolimbic reward system in some women, leading to psychiatric symptoms like anhedonia or psychosis. The Perimenopausal Effects of Estradiol on Anhedonia and Psychosis Study (PEEPs) is a mechanistic clinical trial that aims to (1) identify relationships between perimenopausal-onset anhedonia and psychosis and neuromolecular markers of mesolimbic reward responses and (2) determine the extent to which estradiol treatment-induced changes in mesolimbic reward responses are associated with alleviation of perimenopausal onset anhedonia or psychosis.

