Anhedonia is amongst the most common affective symptoms associated with the menopause transition [13] and is broadly associated with ovarian hormone withdrawal in women and preclinical models of menopause [14]. Whereas psychosis is less common during the menopause transition, late-onset psychotic disorders (e.g., age at onset > 40 years) are twice as prevalent in women [15], with peak psychosis risk around the average age of perimenopause [5]. Both preclinical and human studies have shown an association between greater psychosis-spectrum behaviors and lower estrogen levels in females [5].

Dysfunction in reward salience processing is thought to contribute to both anhedonia and psychosis. Anhedonia is characterized by blunted reactivity to rewards and reduced salience attribution to reward cues [16], processes that are mediated by the mesolimbic dopamine system [17]. Preclinical evidence highlights that dopamine blockade produces anhedonic responses to rewarding stimuli [18]. The magnitude of phasic dopamine release to rewards predicts motivation to work for rewards in humans [19], and those with depression show reduced striatal dopaminergic activity during reward processing [20, 21]. However, other PET studies of dopamine activity in depressed samples have shown mixed findings (e.g., reduced, increased, or similar activity compared to healthy controls), which may be due to heterogeneity of symptoms in samples with major depression [22].

In contrast to the reduced salience attribution to rewards seen in anhedonia, salience attribution to irrelevant stimuli may contribute to psychotic symptoms [16], mediated by aberrant striatal dopamine release [23]. PET imaging studies of psychosis have shown higher baseline dopamine synthesis capacity in psychosis [24] as well as higher spontaneous dopamine release [25]. While distinct profiles of reward system dysfunction contribute to anhedonia and psychosis, dysregulation of the mesolimbic dopamine system may be a common etiological pathway.

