Absent-to-mild psychosis severity is defined in this trial as <6 on the Brief Psychiatric Rating Scale (BPRS) positive symptom subscale [39, 40], consisting of four items: conceptual disorganization, suspiciousness, hallucinations, and unusual thought content. This total indicates a score of “very mild” on any two symptoms or at least mild on any one symptom (control samples typically score absent or “very mild” on these items [46]). “Moderate” psychosis will correspond to BPRS positive symptom subscale scores between 6 and 16, representing one standard deviation above the mean score for patients with psychotic major depression [47]. Additionally, at least one subscale item score must be > 4 to ensure that the psychosis symptom is associated functional impairment. Individuals with psychotic major depression typically have BPRS positive symptom subscale scores between 7 and 11, and a score of 6 best differentiates psychotic MDD from nonpsychotic MDD [47].

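### Objective 1 reports symptom-brain associations as correlations in a sample filled by equal symptom quotas, so r describes the quota sample and, for psychosis, probably exceeds r in eligible women recruited without quotas

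*Protocol article*

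**What the plan says.** Three parts of the protocol article bear on this point.

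- **Estimator.** Statistical methods {20a}, on the baseline objective: "Associations between clinical measures and mechanistic outcomes will be estimated via correlation analysis". Sample size {14} expresses the target effect on the same scale, with a smallest detectable r of .27 for 85 participants at about 80% power, and adds "which is consistent with our in-house pilot data".
- **Sampling.** Eligibility criteria {10}: "equal numbers of participants will be recruited into each of the following four strata". The strata cross two anhedonia levels (SHAPS 20 to 36, and above 36) with two psychosis levels. On the lower psychosis level: "Absent-to-mild psychosis severity is defined in this trial as <6 on the Brief Psychiatric Rating Scale (BPRS) positive symptom subscale". On the moderate level: "psychosis will correspond to BPRS positive symptom subscale scores between 6 and 16", with the further condition that "at least one subscale item score must be > 4".
- **Natural frequency.** Background and rationale {6a}: "Whereas psychosis is less common during the menopause transition". The abstract agrees: "Symptoms commonly include depressed mood and anhedonia and less commonly include psychosis". No percentage is given for moderate psychosis among eligible women.

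The same eligibility section lists a BPRS positive-symptom score between 6 and 17 as an inclusion criterion. Read literally, that excludes the stratum below 6.

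**The concern.** Objectives {7} sets out to characterise the relationship between striatal reward responses and symptoms at baseline, and r is the summary of strength that the plan names. With a fixed slope and a fixed residual spread, r rises with the standard deviation of the symptom score. Equal quotas push the psychosis split to 50:50, which is close to the widest spread that these two groups can give. If moderate psychosis is naturally the minority state among eligible women, the quota widens the spread and raises r without any change in the underlying relationship.

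What is at stake is the reading of the estimate. A reader who takes r as the strength of the link between psychosis and dopamine or BOLD measures in women with perimenopausal-onset symptoms would be reading a figure that the recruitment plan partly determines. For the same reason, r can be compared with the r of another sample only where the symptom spread is similar.

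**Working it through.** **1. The plan's own figure.** Inputs from Sample size {14}: N = 85, r = .27, alpha .05. By Fisher's z, power = Φ(atanh(r)·√(N−3) − z). Here atanh(.27) = .277, √82 = 9.055, product 2.507.
- One-sided: Φ(2.507 − 1.645) = 80.6%, which reproduces the stated value.
- Two-sided: Φ(2.507 − 1.960) = 70.8%, which does not.

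Sidedness is not stated. That is a separate matter; r = .27 serves below only as the reference value.

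**2. Effect of the quota on r for psychosis.** Assumptions, not in the documents: BPRS subscale mean 4.5 (SD 0.5) in the absent-to-mild stratum and mean 10 (SD 2) in the moderate stratum; a linear relation with constant residual SD. With p the share of women with moderate psychosis:

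Var(p) = p·2² + (1−p)·0.5² + p(1−p)·(10 − 4.5)²

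At the quota, p = .5: 2 + 0.125 + 7.5625 = 9.69. With k = √(Var(p)/9.69) and the slope held fixed, r at share p = .27k / √(1 − .27² + .27²k²).

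| Assumed natural share | Var | k | r equivalent to a quota r of .27 |
|---|---|---|---|
| 5% | 1.87 | .44 | .12 |
| 10% | 3.35 | .59 | .16 |
| 20% | 5.84 | .78 | .21 |
| 30% | 7.73 | .89 | .24 |
| 50% | 9.69 | 1.00 | .27 |

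Four other assumed score distributions (low-stratum mean 4.3 to 4.5, moderate mean 8 to 12) gave .12 to .13, .16 to .17, .21 to .22 and .24 to .25 at 5, 10, 20 and 30%. The natural share drives the result; the assumed shape matters little.

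**3. Anhedonia.** With assumed normal SHAPS scores truncated to 20 to 56, a quota r of .27 corresponds to .22 if 10% of eligible women naturally score above 36, .26 if 30% do, and .27 if 50% do. The effect is smaller, and the documents give no direction for the natural share.

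**4. Validity of the test.** Simulating quota sampling with no true association (85 women, two-sided 5% level) gave a rejection rate of 4.8%. The test of r = 0 is sound.

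**5. Which slope is stable.** Varying only the psychosis share left the simple slope unchanged in simulation (.088 to .089 per point). But the quota is set on both symptoms, which makes them roughly uncorrelated in the sample whatever their natural correlation. In general:

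simple BPRS slope = b_P + b_A·Cov(SHAPS, BPRS)/Var(BPRS)

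where b_P and b_A are the slopes with both symptoms in the model. Objectives {7} expects opposite signs for the two symptoms on striatal activation. Illustration with assumed values:
- Source mix: 20% moderate psychosis, 30% high anhedonia, 10% both. The odds ratio is (.10 × .60)/(.10 × .20) = 3.
- Stratum means 5.5 BPRS points and 12 SHAPS points apart; b_P = .09, b_A = −.04.
- Covariance: (.10 − .20 × .30) × 5.5 × 12 = 2.64.
- Simple slope in the source mix: .09 − .04 × 2.64/5.84 = .072.
- Simple slope in the quota sample, where the covariance is about zero: .090.

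The simple slope therefore moves with the quota too. The slopes from the joint model, b_P and b_A, do not.

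**The case against.** The best defence is that nothing in the article is false. Sampling across severity is deliberate and openly described, the Objective 1 hypotheses concern direction only, and no passage presents r as a population quantity. Enrichment also helps power. All of this stands, and it makes the point a matter of how the estimate is defined and labelled. It is nevertheless more than detail left to an analysis plan, because {20a} positively names correlation as the estimator.

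The second defence is that the size is assumed. That also stands. The remark that psychosis is less common concerns the transition in general, whereas eligible women already have SHAPS scores of at least 20; their natural share of moderate psychosis is unknown, and at 30% the shift is only from .27 to .24.

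Three stronger readings may tempt a reader, and the documents support none of them.
- **Later trials would be too small.** The background section speaks of imaging targets for mechanistic trials in perimenopausal-onset disorders. It plans no study of unselected women sized on a baseline r.
- **Reweighting to natural frequencies is available from the screening log.** Data management {19} describes counts of women pre-screened, consented, cleared, completed and withdrawn; it does not say that symptom strata are recorded. Recruitment through advertisements and clinics, psychiatry among them, would not give population frequencies in any case.
- **The agreement with pilot data is misplaced.** How the pilot was sampled is not shown, so nothing follows either way.

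**Conclusion.** The point holds in a limited form. The Objective 1 r is specific to the quota sample. For psychosis it probably exceeds the r in eligible women recruited without quotas, provided that moderate psychosis is naturally present in fewer than half of them, that the relation is roughly linear with constant residual spread, and that women below 6 on the BPRS subscale are in fact enrolled. Under the assumed distributions, the r without quotas that matches a quota r of .27 runs from about .12 (5% natural share) to .24 (30%); the documents do not say where in that range, or outside it, the truth lies. The test of no association and its power are unaffected. This is a minor improvement to the reported estimate and no threat to the trial.

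The condition on enrolment rests on unreconciled text. The 6 to 17 inclusion range would empty the lower stratum, while the abstract, Trial design {8} and the strata themselves all describe psychosis from absent upwards.

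**What to change.** In Statistical methods {20a}, replace the sentence on estimation by correlation with one to this effect: for each striatal measure, the Objective 1 estimates are the unstandardised slopes per SHAPS point and per BPRS subscale point, with 95% confidence intervals, from a linear regression containing both scores; correlations are also reported and describe the quota-stratified sample only.

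Both scores must be in the model because the quota is set on both jointly. The planned test of r = 0 may stay as it is, so its power statement is untouched. The cost is one sentence, with no new data.

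Separately, reconcile within Eligibility criteria {10} the BPRS inclusion range of 6 to 17, the stratum below 6 and the moderate stratum of 6 to 16. The condition of one item above 4 belongs in the same check: if items start at 1, the lowest total that meets it is 5 + 1 + 1 + 1 = 8, so totals of 6 and 7 fall in neither stratum.
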